#### 11.2.4. Data Types

The instruments to be used in this proposed study include a demographic data sheet, an electronic questionnaire (e-questionnaire), an online checklist, and equipment for counting bacteria on hands and for respiratory virus testing. The information collected by the demographic data sheet will include the schoolchildren’s age and medical history. The e-questionnaire will measure the schoolchildren’s hand-hygiene compliance and awareness of hand-hygiene practice, and their participation in SARS-CoV-2 screening. The online checklist will record the schoolchildren’s hand-hygiene practices and their performance in gargle collection. The bacterial counts will serve as a measure of the bacterial loads on the schoolchildren’s hands. The results of respiratory virus testing will indicate the rates of upper respiratory tract infection in the schoolchildren.

##### Hand-Hygiene Compliance (T1, T2, T3 and T4)

A hand-hygiene compliance checklist [59] will be used to measure the extent of hand-hygiene compliance in the intervention and control groups. Higher scores indicate better performance.

##### Awareness of Hand-Hygiene Practice (T1, T2, T3 and T4)

Schoolchildren’s knowledge of hand-hygiene practice will be measured. To profile their prior knowledge and their level of understanding after the programme, 10 ‘true or false’ questions on hand hygiene adapted from the American Cleaning Institute in 2011 will be administered to both the intervention and control groups. This instrument presents a good content validity index of 0.86 and a good two-week test–retest reliability of 0.75 [60].

Schoolchildren’s rate of participation in SARS-CoV-2 screening (T1, T2, T3 and T4)

The number and percentage of children participating in SARS-CoV-2 screening, and their reasons for doing or not doing so, will be collected.

Bacterial loads on hands (T1, T2, T3 and T4)

The research team will collect swabs of the schoolchildren’s hands to calculate the total bacterial counts of the intervention and control groups. Collections will be performed after school hours.

Reverse transcription–polymerase chain reaction testing for SARS-CoV-2 and other respiratory viruses (at T1, T2, T3 and T4, and at any time schoolchildren exhibit a fever with upper respiratory-tract infection symptoms)

Gargle samples will be collected from the children for RT-PCR tests for SARS-CoV-2, influenza A and B viruses, respiratory syncytial virus, rhinoviruses and adenoviruses. Testing for SARS-CoV-2 in gargle samples will be out-sourced to a company or organisation that provides a high-quality service.

#### 11.2.5. Data Analysis

Descriptive statistics will be used to present all of the demographic, programme attendance and outcome data. Chi-square or independent sample *t*-tests (for categorical and interval data, respectively) will be used to identify the heterogeneity of demographic and baseline data in the two groups and settings. The effectiveness of the VRG-based educational intervention on the primary outcomes (the level of knowledge and practice, the bacterial loads and the detection rates of respiratory viruses) will be examined by linear mixed-effect modelling to compare changes in the primary outcome values of the intervention and control groups over time (from baseline to the two post-tests) on an intention-to-treat basis, using repeated-measures analysis of covariance, multivariate analysis of covariance and/or mixed modelling techniques.

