### 11.1. Aims

The proposed project will aim to investigate the ability of a virtual reality game (VRG)-based educational intervention to enhance primary schoolchildren’s compliance with hygiene practices and increase their participation in SARS-CoV-2 screening, to prevent SARS-CoV-2 transmission in the community. The objectives are as follows.

To assess the ability of a VRG-based educational intervention to enhance the knowledge and hygiene-practice compliance of primary schoolchildren in terms of the prevention of SARS-CoV-2 transmission, in comparison with a control group receiving usual community care, at 6 months after the intervention.To compare the bacterial loads on primary schoolchildren’s hands between the study group and the control group at 6 months after the intervention.To compare the detection rates of SARS-CoV-2 and other respiratory viruses in primary schoolchildren’s throat gargle samples between the study group and the control group at 6 months after the intervention.To compare the number of schoolchildren who participate in the community SARS-CoV-2 screening programme between the study group and the control group at 6 months after the intervention.

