#### 11.2.1. Subjects

Primary schoolchildren will be recruited from local primary schools. The eligibility criteria will be (1) primary school children aged 6–12, and (2) able to communicate in Chinese and to read Chinese. The exclusion criteria will be (1) reported mental or physical health disorders and (2) engagement in other health educational programmes related to hygiene practices 2 months or less before recruitment. The school management staff will help us to liaise with the schoolchildren and refer them to the research team. Informed consent will be obtained from school principals, parents and schoolchildren before the study begins. To minimise selection bias, the children will not be informed of whether they will join the intervention group or the control group. Potential subjects will be screened and recruited in these schools by the research team. In order to avoid data contamination in the control group, school children who have siblings in the intervention group will not be recruited. Details of the study will be provided to the schools, the schoolchildren and their parents. Sample size has been computed to obtain a statistical power of no less than 0.8 to detect the significance of the four objectives with continuous outcomes at a 0.05 level of significance. With 0.2 as the Cohen’s d effect size and under balanced allocations, we have set the intra-cluster correlation to 0.05, the correlation among level-2 units nested in a cluster to 0.01, the number of level-1 units to 30, and the sample size of level-2 stratified units to 2, we have 18 school clusters in each arm. Therefore, the sample size should be 2160.

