## 12. Across All Studies, Other Common Elements Include

Stop-and-go criteria [39] will be used in terms of subject recruitment (<20% vs. >50% meeting eligibility criteria, respectively); intervention acceptability (<30% vs. >60 or >70%, respectively, in different studies), and loss to follow up (<30% vs. >70 or >80%, respectively, in different studies). Furthermore, the RE-AIM framework [61] will be used to guide the evaluation of all studies. We will collect metrics on Reach (e.g., number of website visits), Effectiveness (changes in stay-at-home motivation and intention or changes in hygiene practice), Adoption (e.g., the amount of content created by the public with the campaign hashtag), Implementation (e.g., consistency in implementation of the educational VRG), and Maintenance (e.g., number website visits after the programme) as appropriate, to document formative and summative impact. All analyses will be performed using SPSS 26.0 software and a *p* value < 0.05 will be considered statistically significant.

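### Study 5 tests three or four primary outcomes, each at 0.05, with no order, alpha split or success rule, although 2160 children give 80% power for one outcome only

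*Protocol article*

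**What the plan says.** All references are to the protocol article.

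- **Primary outcomes (11.2.5 Data Analysis).** The analysis covers "the primary outcomes (the level of knowledge and practice, the bacterial loads and the detection rates of respiratory viruses". The methods are an open and/or list of repeated-measures ANCOVA, multivariate ANCOVA and mixed modelling. No outcome is ranked above another.
- **Sample size (11.2.1 Subjects, Study 5).** The aim is "statistical power of no less than 0.8 to detect the significance of the four objectives with continuous outcomes at a 0.05 level of significance". The inputs are given: "With 0.2 as the Cohen’s d effect size and under balanced allocations", and "we have set the intra-cluster correlation to 0.05, the correlation among level-2 units nested in a cluster to 0.01". There are 30 children per grade stratum, two strata per school and 18 schools per arm, which makes 2160 children.
- **Objectives (11.1 Aims).** There are four, all at 6 months after the intervention: knowledge together with hygiene compliance; bacterial load on the hands; virus detection; and, fourth, "To compare the number of schoolchildren who participate in the community SARS-CoV-2 screening programme between the study group and the control group".
- **Threshold (section 12).** For all five studies, "All analyses will be performed using SPSS 26.0 software and a *p* value < 0.05 will be considered statistically significant".
- **Comparison (9.2.2, Study 3).** The same article sizes Study 3 at alpha 0.0042 to hold the overall type 1 error at 0.05 over 12 outcomes.

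**The concern.** When several outcomes are all primary, the plan has to say how they combine into a conclusion. Study 5 does not say whether one significant outcome is enough, whether all are needed, or whether one comes first. A mixed result, such as better knowledge with unchanged bacterial load, therefore has no defined meaning.

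The two natural readings each conflict with something the plan wants. If one success is enough, the chance of a false claim exceeds 5%. If all must succeed, the stated power is not reached. Multivariate ANCOVA is only one of several optional methods, so it does not act as a global gate.

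The set of outcomes is also unsettled. The sample size text says that four objectives are covered, but the primary list matches only the first three.

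**Working it through.** **Inputs from the plan:** d = 0.2; correlations 0.05 (within stratum) and 0.01 (between strata of a school); 30 children per stratum; 2 strata per school; alpha 0.05; power 0.8. Sidedness is not stated for Study 5, but two-sided reproduces the stated size. **Assumed:** the correlation between outcomes, which the article does not give. I use 0 to 0.8, equal for all pairs, with normal test statistics.

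**1. Reproduce the stated size.**
- Design effect = 1 + (30 − 1) × 0.05 + 30 × (2 − 1) × 0.01 = 1 + 1.45 + 0.30 = 2.75.
- Schools per arm = 2 × 2.75 × (1.960 + 0.842)² / (60 × 0.2²) = 5.5 × 7.849 / 2.4 = 17.99, rounded up to 18.
- Children = 18 × 2 × 60 = 2160, which matches the plan.
- Power = Φ(0.2 × √(1080 / 5.5) − 1.960) = Φ(2.803 − 1.960) = 0.800.

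This is the size for one continuous outcome at two-sided 0.05. It contains no allowance for a second outcome.

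**2. Count the outcomes.** Section 11.2.4 gives hand-hygiene compliance and knowledge their own instruments, which supports four. Section 11.1 puts them in one objective and section 11.2.5 lists them as one item, so three is also a fair reading.

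**3. If any one significant outcome is enough.** With independent tests the chance of at least one false positive is 1 − 0.95^k: 1 − 0.95⁴ = 18.5% and 1 − 0.95³ = 14.3%. With correlated tests, by numerical integration:

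| Assumed correlation | Three outcomes | Four outcomes |
|---|---|---|
| 0 | 14.3% | 18.5% |
| 0.3 | 13.6% | 17.4% |
| 0.5 | 12.5% | 15.6% |
| 0.8 | 9.8% | 11.4% |

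If screening participation were added as a fifth primary outcome, the range would be 22.6% to 12.7%.

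**4. If all four must succeed.** The error rate does not exceed 5%. Joint power, with a true effect of d = 0.2 on every outcome, is 0.80⁴ = 0.41 if independent, 0.56 at correlation 0.5 and 0.66 at 0.8.

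**5. If alpha is divided.** With 18 schools per arm, power for an outcome is Φ(2.803 − z), where z is the two-sided critical value at 0.05/k:
- three outcomes (alpha 0.0167): Φ(2.803 − 2.394) = 0.66;
- four (alpha 0.0125): Φ(2.803 − 2.498) = 0.62;
- five (alpha 0.01): Φ(2.803 − 2.576) = 0.59.

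Bonferroni at 80% power would need 24 schools per arm (2880 children) for three outcomes, or 26 (3120 children) for four.

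**The case against.** The best defence has four parts.

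*No rule says that one success is enough.* This is true. The objectives are distinct and could be reported separately, so the inflation in step 3 is conditional. But no other rule is stated either, and requiring all four moves the problem to power.

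*The threshold in section 12 is a blanket line, and an analysis plan that is not shown could set the order.* The line does coexist with an adjusted alpha in Study 3, so on its own it is weak evidence that no adjustment is intended. The stronger evidence is section 11.2.1, which sets 0.05 for Study 5 and derives the sample size from it. A fixed order added elsewhere would be compatible with that size; a division of alpha would not.

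*The size of the inflation is not known.* This stands. A reader might quote one figure, such as 16%, or say three times the nominal rate. For four outcomes 16% needs a correlation of about 0.46, which the article does not supply. Only a range is defensible.

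*An objective may be secondary.* This also stands. A reader might infer that sections 11.1 and 11.2.5 contradict each other over screening participation. They do not, because nothing says that every objective is primary. What remains is an inconsistency of labelling with the claim that four objectives are powered.

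A reader might also add further inflation from separate tests at T2, T3 and T4. The article does not support this: every objective names 6 months, and section 11.2.5 describes change over time in a model, not a test at each visit.

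**Conclusion.** The point holds in conditional form. Study 5 has three or four primary outcomes at 0.05 each, no rule that joins them, and a sample size that gives 80% power for one outcome.

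- If any one may carry the claim, the false-claim probability is about 11% to 19% for four outcomes, or 10% to 14% for three.
- If all four must succeed, there is no inflation, but joint power is about 0.41 to 0.66, short of the 0.8 in section 11.2.1.

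The ranges rest on an assumed correlation between outcomes of 0.8 to 0, equal across pairs. The power figures also take d = 0.2 and the plan's design effect for every outcome. Under either rule, what the plan says about error or about power fails, so the sponsor has to choose a rule. The status of screening participation is a separate, smaller matter of reconciliation.

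**What to change.** 1. Name 6 months (T4) as the primary time point, as every objective in section 11.1 already does, and call T2 and T3 supportive. This also settles section 11.2.5, which speaks of two post-tests where section 11.2.3 has three.
2. State in section 11.2.5 that the primary outcomes are tested in a prespecified fixed sequence, each at two-sided 0.05, and that confirmatory claims stop at the first non-significant result. The sponsor sets the order before any data are seen. The order in section 11.1 is knowledge, hygiene compliance, bacterial load, virus detection, and then screening participation if it is primary.
3. Reconcile sections 11.1, 11.2.1 and 11.2.5 by labelling screening participation primary or secondary, and say whether knowledge and practice are one outcome or two.
4. Reword the power statement in section 11.2.1 so that 0.8 refers to a single outcome at two-sided 0.05.

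**Cost.** Wording only; the sample size stays at 2160. The price is that later outcomes lose confirmatory status if an earlier one fails, so the first place in the order matters most. If no order can be agreed and Holm is used instead, the power at its first step should be restated as about 0.66 for three outcomes, 0.62 for four or 0.59 for five.

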##### Phase 2: Main Study (40 Months)

Intervention group: Educational intervention using a VRG over 3 weeks.

The schoolchildren in the intervention group will take part in an innovative VRG-based educational programme featuring: (1) Web-based health education on (i) SARS-CoV-2 transmission, (ii) proper hand and respiratory hygiene practices and (iii) the importance of community SARS-CoV-2 screening and throat-gargle collection procedures; (2) built-in instant feedback on their performance of hygiene practices; and (3) a chat function for efficient nurse–parent–schoolchild interactivity and communication. The schoolchildren will receive three sessions (one per week) of the VRG-based educational programme, which will be provided by the research team during extracurricular activity time. Each session will consist of two VRGs and will last 30–45 min. Six VRGs will be designed, representing six ascending levels. After completing each level, schoolchildren will be granted access to the next level. This design will engage the schoolchildren in playing the VRGs. Levels 1 and 2 will address the fundamentals of SARS-CoV-2 transmission and hand hygiene; levels 3 and 4 will consist of family-based scenarios exemplifying the chain of infection and throat gargle collection; and levels 5 and 6 will address how to combat germs in school-based scenarios and the importance of community SARS-CoV-2 screening. The schoolchildren will be required to complete electronic questionnaires pre-post and 3 months and 6 months after they participate in the educational programme. Parents will use the online checklist provided to assess schoolchildren’s performance on the return-demonstration of hand hygiene and throat gargle pre–post, and 3 months and 6 months after the educational programme. To ensure the accuracy of the recordings of the schoolchildren’s hygiene practices, the return-demonstration will be video-recorded and uploaded to the online platform by parents, for analysis by the research team.

Control group. The schoolchildren in this group will receive the usual health education or care available in the community. The VRG equipment will not be made available to the schoolchildren in this group within the intervention period.

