#### 11.2.3. Study Design

The duration of each schoolchild’s involvement in the study will be 6 months, with assessments at baseline before the intervention (T1), immediately after the intervention (T2), at 3 months after the intervention (T3), and at 6 months after the intervention (T4). It is proposed that 12 schools will participate in the study every 12 months, and thus it will take 36 months to complete the intervention in 36 schools. Four months will be used for data cleaning, analysis and report writing. Data will be collected at four time-points, T1, T2, T3 and T4, to test the sustained intervention effect.

Randomisation: A large-scale stratified cluster RCT will be undertaken. Primary schoolchildren will be recruited via local conventional school clusters from 18 districts in Hong Kong, which have been chosen to provide a geographically representative sample. The cluster sizes will be equal across school clusters. We will select 36 primary schools and will randomly assign them to the intervention group or the control group in a ratio of 1:1. To adjust for age as a confounding factor, the schoolchildren from each school cluster will be separately drawn from lower grades (Primary 1 to 3) and higher grades (Primary 4–6). Therefore, we have designed a three-level hierarchical mixed model that is randomised at the third level. Here, a school is considered to be a level-3 cluster, the grades within a school are considered to be level-2 stratified units and the schoolchildren in our trials are considered as level-1 units [58].

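### Study 5's analysis section counts two post-tests where the design has three, and does not tie the test to the 6-month comparison that all four objectives ask for

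*Protocol article*

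**What the plan says.** Section 11.2.5 (Data Analysis) examines the primary outcomes, namely knowledge and practice, bacterial load and respiratory virus detection, by comparing "changes in the primary outcome values of the intervention and control groups over time (from baseline to the two post-tests". The basis is intention to treat. The method is linear mixed-effect modelling, with repeated-measures ANCOVA, MANCOVA and mixed modelling listed as alternatives or in combination.

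The design sections give a different visit count:

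- Section 11.2.3 (Study Design) schedules a baseline and then assessments "immediately after the intervention (T2), at 3 months after the intervention (T3), and at 6 months after the intervention (T4". It adds: "Data will be collected at four time-points, T1, T2, T3 and T4, to test the sustained intervention effect".
- Phase 2: Main Study has the children complete "electronic questionnaires pre-post and 3 months and 6 months after they participate in the educational programme".
- The outcome headings under 11.2.4 (Data Types) list T1, T2, T3 and T4 for every outcome.

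Section 11.1 (Aims) sets the first objective "in comparison with a control group receiving usual community care, at 6 months after the intervention". The other three objectives name the same 6-month time.

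**The concern.** Three post-tests are collected and two are analysed, and the text does not say which two. If they were T2 and T3, the analysis would leave out the only visit that the objectives name. If they include T4, the 6-month comparison is one part of a change-over-time analysis, and nothing says that it decides the result.

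The intervention is three weekly sessions, and the follow-up exists to see whether the effect lasts. An effect that is strong just after the sessions and weak at 6 months is therefore a pattern the trial should be able to tell apart from a lasting one. A test that leans on the earlier visits could succeed under that pattern, and the 6-month objectives could be reported as met. If the choice of visits stays open until outcomes are seen, the results could also guide it.

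**Working it through.** **1. Visit count**

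| Place | Post-tests |
|---|---|
| 11.2.3 Study Design | 3 (T2, T3, T4) |
| Phase 2: Main Study | 3 (post, 3 months, 6 months) |
| 11.2.4 outcome headings | 3 (T2, T3, T4) |
| 11.2.5 Data Analysis | 2, not identified |

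The objectives in 11.1 at 6 months (T4) number 4 of 4. The two post-tests could be T2+T3, T2+T4 or T3+T4. One of these pairs omits T4 and two include it.

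**2. The plan's sample size** (inputs from 11.2.1 Subjects: d = 0.2, correlations 0.05 and 0.01, 30 children in each of 2 grade strata per school, power 0.8, alpha 0.05, taken as two-sided)

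- Design effect: 1 + (30 − 1) × 0.05 + 30 × (2 − 1) × 0.01 = 2.75
- Schools per arm: 2 × (1.960 + 0.842)² × 2.75 / (0.2² × 30 × 2) = 17.99, rounded up to 18
- N = 2 × 18 × 2 × 30 = 2160, with power 80.0%

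The stated figure is reproduced. The formula has no repeated-measures term, so it fits a single arm contrast at one time, such as T4. Correcting the visit wording leaves N unchanged.

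**3. Illustration of what the choice of visits can do.** The effect patterns and the between-visit correlation (0.4 to 0.6) are assumptions. So is the use of a simple average over visits, since 11.2.5 does not state one. Normal approximation throughout.

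- Standard error of d at one visit: 2 × √(2.75 / 2160) = 0.0714
- Average of two visits: 0.0714 × √((1 + ρ)/2) = 0.0597 (ρ = 0.4) to 0.0638 (ρ = 0.6)
- Average of three visits: 0.0714 × √((1 + 2ρ)/3) = 0.0553 to 0.0611
- Chance of significance: Φ(effect / SE − 1.96), or 5% where the true effect is zero

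| Assumed effect at T2 / T3 / T4 | T2+T3 | T2+T4 | T3+T4 | All three | T4 alone |
|---|---|---|---|---|---|
| 0.4 / 0.2 / 0 | over 99% | 88–92% | 35–39% | 91–95% | 5% |
| 0.3 / 0.2 / 0.1 | 97–99% | 88–92% | 65–71% | 91–95% | 29% |
| 0.2 / 0.2 / 0.2 | 88–92% | 88–92% | 88–92% | 91–95% | 80% |

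In the last row every reading targets the same effect, 0.2, and only precision differs. In the first two rows the readings target different quantities.

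**The case against.** The strongest reply is that this is a slip of one word. The Aims fix the time at 6 months, every outcome is collected at T4, and two of the three possible pairs contain T4. A plan to discard the one visit that every objective names is unlikely. This stands: a reader might infer that T4 is left out of the analysis, but the documents support that only as one possible reading.

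It can also be said that an article commonly leaves the exact model contrast to a fuller document, and that a mixed model with a group-by-time term yields a T4 contrast anyway. That is fair as far as silence goes. But 11.2.5 is not merely silent. It states a visit count that the rest of Study 5 contradicts, and correcting the count alone would still leave a change-over-time comparison that is not tied to the 6-month objectives.

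Two further inferences are tempting and do not hold. Because "the schoolchildren in our trials are considered as level-1 units", a reader might conclude that the three-level model has no room for repeated visits. That hierarchy describes the clustering. Section 11.2 calls the trial a repeated-measures design, and a within-child covariance handles the visits without a further level. A reader might also see a conflict between 6 months of involvement per child and a T4 that falls 6 months after a 3-week course. That is a rounded duration with no bearing on the analysis, since T4 is explicitly scheduled.

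Finally, the power figures rest on assumed decay and on visit averages that the plan does not state. They show what could happen and do not predict it.

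**Conclusion.** The point holds as an internal contradiction. The analysis section counts two post-tests, the design has three, and as written the analysis does not secure the 6-month arm comparison set by all four objectives. It should be fixed, ideally before outcome data are seen.

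The consequence is conditional. If the effect fades, a test that draws on earlier visits can be significant in most trials while the 6-month effect is small or absent. Under the assumed patterns, the T2+T3 average gives 97% or more against 5% to 29% for T4 alone. If the effect is constant, nothing is lost by any reading. The documents do not show that T4 will be omitted. The sample size, the data collected and the clustering structure are untouched.

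**What to change.** In 11.2.5, replace the reference to two post-tests with the three post-tests (T2, T3, T4), and add wording along these lines:

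*The primary test for each outcome is the difference between arms at T4, adjusted for the T1 value, from a mixed model that accounts for school, grade within school and repeated visits within child, with a suitable link for binary outcomes such as virus detection. Contrasts at T2 and T3 are secondary.*

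A joint model of all visits with a T4 contrast serves as well as a model of T4 alone, and can use children with partial follow-up. The link matters because linear modelling is the only form now named, while virus detection is a yes/no result per child. The cost is a sentence or two, with no new data and no change to N.
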